#### Control

On the maxillary and mandibular arches of the contralateral side, no laceback is placed. This serves as the control and henceforth is termed as “no laceback side.” Figure 3 explains the CONSORT flowchart for this study.

**Figure 3. F3:**
[figure not shown]
CONSORT (Consolidated Standards of Reporting Trials) flowchart.

### Data Collection

#### Primary Outcome: Plaque Score

Plaque score is recorded to assess the patient’s oral hygiene status. For this study, the OPI by Beberhold et al [32] is chosen. The OPI is scored by visually examining whether dental plaque has accumulated at the tooth surface adjacent to each side of the bracket base (mesial, distal, occlusal or incisal, and gingival). The condition of the gingival margin is also noted. A score of 0 to 4 is given according to the criteria given in Figure 4. A higher plaque score indicates a poorer oral hygiene status.

**Figure 4. F4:**
[figure not shown]
Criteria for Orthodontic Plaque Index scores.OPI: Orthodontic Plaque Index.

Plaque score is recorded on the laceback and no laceback side during T_0_ (before laceback placement during first review appointment 1 wk after bond-up) as baseline, T_1_ (4 wks after laceback placement), and T_2_ (4 wks after T_1_). Once intervention starts at T_0_, if a participant cannot attend T_1_ or T_2_ appointments, a maximum of 2 weeks’ leeway is given, corresponding to the normal orthodontic follow-up interval of 6 weeks between appointments.

During T_0_, T_1_, and T_2_, archwires and lacebacks (if present) are removed, and plaque disclosing agent (GC Tri Plaque ID Gel; GC Asia Dental) is applied on the buccal surfaces of upper and lower canines, premolars, and first molars. Then, plaque score is recorded on those teeth by a blinded clinician not involved in the treatment of the participant. The tooth surface adjacent to each side of the bracket (mesial, distal, occlusal or incisal, and gingival) is visually examined for accumulation of plaque. The average OPI for the laceback and no laceback side is calculated by adding up the plaque score of all the teeth recorded on each side and dividing it by the number of teeth scored. The maximum plaque score for each side is 4, and the minimum score is 0. The criteria for scoring are explained in Figure 4 [32].

#### Examiner Calibration and Reliability Assessment

Inter- and intrarater reliability assessments of OPI were done before the trial commenced. Calibration of OPI was done on 20 orthodontic patients not participating in the trial. Using a Canon EOS RP digital camera (Canon Inc.) with RF100mm f/2.8L MACRO IS USM lens (Canon Inc.) and Godox Macro Ring Flash ML-150II (GODOX Photo Equipment Co., Ltd.) for illumination, buccal view intraoral photographs of these patients involved in the calibration exercise were also taken after application of plaque disclosing agent (GC Tri Plaque ID Gel; GC Asia Dental). Then, intrarater reliability was assessed by scoring 10 randomly selected photographs printed on photographic paper and rescoring them after 2 weeks. Reliability assessments were measured using Cohen kappa. The threshold was set to be more than 0.8 for this study, indicating good inter- and intrarater reliability [33].

#### Secondary Outcomes: Frequency of Archwire Complications

Archwire complications include the following:

Archwire fractured at any part distal to the canine bracket: counted as 1 incident.Archwire dislodged from one or more canine brackets, premolar brackets, or first molar tubes: counted as one incident.Archwire permanently deformed at any part distal to the canine bracket: counted as 1 incident.Any combination of the above 3 situations is counted as 1 incident.The whole archwire is lost: counted as 1 incident each on both laceback and no laceback sides.

The frequency of archwire complications on the laceback side and the no laceback side is recorded. The time points for recording are during T_1_, T_2_, and whenever a participant comes for an emergency appointment between T_0_ and T_2_. The number of complications on the upper and lower archwires is recorded separately and summed up for the laceback side and the no laceback side. During emergency appointments, dislodged archwires are religated using elastomeric modules and reinserted into the buccal tubes, whereas broken archwires are replaced by the same type of archwire. During T_1_ and T_2_ appointments, after data collection for archwire complications, archwires are removed to facilitate plaque score recording. After T_2_ data collection is completed, the treating clinician religates new or existing archwires according to their preference, as the trial would have ended.

#### Secondary Outcomes: Frequency of Laceback Complications

Laceback complications include the following:

Laceback ligature fractured at any part is counted as 1 incident.Laceback ligature dislodged from 1 or more brackets of canine, premolar, and first molar hooks is counted as 1 incident.A combination of the above 2 situations is counted as 1 incident.The whole laceback is lost is counted as one incident.

Frequency of laceback complications is recorded. The time points for recording are during T_1_, T_2_, and whenever a participant comes for an emergency appointment between T_0_ and T_2_. Upper and lower lacebacks are visually examined during the appointment. The number of complications on the upper and lower lacebacks is recorded separately and summed up. The total number of laceback complications throughout the study period (T_0_ to T_2_) is recorded. During emergency appointments, dislodged lacebacks are retied from the first molar hook to the canine bracket using the same protocol described previously, whereas a broken or missing laceback is replaced using new but the same type of preformed 0.010-inch stainless steel wire ligature in the same manner. During T_1_ and T_2_ appointments, after data collection for laceback complications, lacebacks are removed to facilitate plaque score recording. After T_2_ data collection is completed, the treating clinician religates archwires with or without lacebacks according to their preference, as the trial would have ended.

#### Secondary Outcomes: Pain

Pain is recorded using the Visual Analog Scale, as it is the most widely used pain assessment scale and is suitable to be applied to the current age group of recruited participants. Pain score is recorded by the study participants on both laceback and no laceback sides. During T_0_, before placing lacebacks, the pain score is first recorded on both sides as baseline. Participants are given a pain diary to bring home during T_0_ and another copy during T_1_. At home, participants are reminded via mobile phone messaging (WhatsApp; Meta) to complete the pain diary. The pain diary given during T_0_ is collected back during T_1_ and T_2_. Participants are asked to rate the maximum pain experienced on each side during specific time points throughout the period between T_0_ and T_1_ and between T_1_ and T_2_. The time points are: 4 hours, 24 hours, 3 days, 1 week, 2 weeks, 3 weeks, 4 weeks from the review appointment. The 4-week time point can be recorded during the T_1_ or T_2_ appointment itself, or if the participant is unable to turn up for the appointments, they should record the pain score for the 4-week time point at home. Participants are instructed to place a mark along a 100-mm horizontal line at the most relevant position, whereby the left extreme indicates “no pain and discomfort” and the right extreme indicates “worst imaginable pain and discomfort.” Visual Analog Scale is measured to the nearest 1 mm using a standard metal ruler from the scale’s zero point to the patient’s mark and therefore quantified in a score with a range of 0 to 100. Each pain score reading is accompanied by an open-ended question asking what the cause of pain is (if any). Participants are informed that the pain recorded should arise from the laceback. Analgesics should not be taken prophylactically. If an analgesic is taken, the score should reflect the maximum pain experienced before taking the analgesic.

While there is a small risk of spill-over effect in this split-mouth study when recording pain score due to the occasional radiating nature of pain, this is minimized through patient education about pain localization. Prior to study commencement, participants will be explained about the different possible causes of pain during orthodontic treatment. Participants will be taught to look out for pain caused by the orthodontic appliance; for instance, long ligature wires rubbing on the cheek and twisted ends of laceback, which are pointed and poking on the oral mucosa. Participants are reminded to check their appliance in front of a mirror twice daily for breakages and identify areas on the left and right sides of their mouth that are sore from the orthodontic appliance.

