### Intended Statistical Analysis

Statistical analysis is conducted using IBM SPSS Statistics (version 31). Descriptive statistics are used to report participant demographics, baseline characteristics, and frequency of laceback complications. To assess whether the data are normally distributed, interpreting the shape of the histogram and the Shapiro-Wilk test are used. Intra- and interrater reliability for plaque score assessment are measured using Cohen kappa. The threshold for good inter- and intrarater reliability is set to be more than 0.8.

Repeated outcome measurements of plaque scores will be analyzed using a mixed model for repeated measures. The model includes treatment group, time, and treatment-by-time interaction as fixed effects, with participant included as a random effect. A mixed model for repeated measures allows inclusion of participants with incomplete follow-up data without requiring formal imputation, assuming data are missing at random. If the data are not normally distributed, plaque scores over time (T_0_, T_1_, and T_2_) will be compared using the Friedman test.

From the pain diary gathered, the pain scores are plotted against time to allow calculation of area under the curve (AUC) using the trapezoidal rule [34]. Pain AUC will be calculated between T_0_ and T_1_ and T_1_ and T_2_. The mean pain AUC for laceback and no laceback sides will be calculated by averaging pain AUC values between T_0_ and T_1_ and between T_1_ and T_2_. To compare differences in mean pain AUC of laceback and no laceback groups, a paired *t* test is used if data are normally distributed. If the normality assumption is violated, the Wilcoxon signed-rank test is applied instead.

The mean frequency of archwire complications is recorded by summing up the number of complications that happen throughout the study period from T_0_ to T_2_. To compare differences in the mean frequency of archwire complications between the laceback and no laceback groups, a paired *t* test is used if data are normally distributed. The mean frequency of laceback complications and the number and percentage of participants with at least 2 laceback complications are also reported. The value of *P*<.05 is considered statistically significant.

Sensitivity analysis will be conducted by comparing the results of intention-to-treat and per-protocol analyses. If both analyses yield similar results, this demonstrates the robustness and validity of the study’s conclusions.

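### Unblinded participants are told to record pain arising from the laceback while scoring both sides, which biases the secondary side-to-side pain comparison against the laceback

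*Protocol article*

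**What the plan says.** All of the following is in the Methods of the protocol article.

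- **Who scores what.** Secondary Outcomes: Pain states: "Pain score is recorded by the study participants on both laceback and no laceback sides". It adds: "Participants are asked to rate the maximum pain experienced on each side during specific time points". For the start of follow-up it says: "During T_0_, before placing lacebacks, the pain score is first recorded on both sides as baseline".
- **What may be recorded.** The same section says: "Participants are informed that the pain recorded should arise from the laceback". No side is exempted. Each reading also carries an open question about the cause of the pain.
- **Training.** The next paragraph of that section says: "Participants will be taught to look out for pain caused by the orthodontic appliance". It gives ligature wires and twisted laceback ends as examples, and asks participants to locate sore areas on left and right.
- **Control.** "On the maxillary and mandibular arches of the contralateral side, no laceback is placed".
- **Blinding.** Participants are not blinded to side.
- **Analysis.** Intended Statistical Analysis computes an AUC per side and uses a paired t test, or the Wilcoxon signed-rank test if normality fails: "To compare differences in mean pain AUC of laceback and no laceback groups". It gives no role to the answers on cause.

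**The concern.** A paired comparison of sides is interpretable only if the same question is asked of both. Here the admissible answer depends on whether the intervention is present. On the laceback side a participant can attribute background soreness from archwire or brackets to the laceback and mark it. On the control side the same soreness has no laceback to be attributed to, so the instruction gives no reason to mark it.

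What is at stake is the trial's only patient-reported outcome and one of its four stated objectives. The Discussion expects slightly more discomfort on the laceback side and wants the result to inform patient counselling. The instruction pushes the data in that expected direction. The problem also lies in data collection: no later analysis can recover pain that was never marked.

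**Working it through.** **1. The plan's own figure.** The only sample size stated is for the plaque index. The standardised paired difference is dz = 1 / 1.88 = 0.532. With a two-sided paired t test at 0.05 (noncentral t, noncentrality dz × √n), n = 34 gives 85.3% power, and 34 / 0.90 = 37.8, rounded up to 38. Both stated numbers reproduce and are untouched by this point. No effect size, SD or power is stated for pain.

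**2. Literal compliance.** Let L and C be the recorded AUCs on the laceback and control sides. If only laceback pain is admissible, C = 0 at every time point and the paired difference is L − C = L, which cannot be negative. Two things follow:

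- Any background pain on the laceback side that is put down to the laceback enters as an effect.
- A benefit of the laceback cannot appear. Pain from a dislodged archwire on the control side is not recorded, although the Discussion hypothesises fewer archwire complications with a laceback.

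**3. Illustration with control at 0.** Assume no true difference between sides. Pain wrongly attributed to the laceback has mean m and SD s across participants, on the VAS in mm, and C = 0. Then dz = m / s, and the rejection rate is the power of the two-sided paired t test at that dz. All values of m and s are assumptions.

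| m / s (mm) | dz | n = 38 | n = 34 |
|---|---|---|---|
| 3 / 6 | 0.500 | 85.1% | 80.8% |
| 5 / 10 | 0.500 | 85.1% | 80.8% |
| 3 / 8 | 0.375 | 61.5% | 56.5% |
| 2 / 6 | 0.333 | 51.7% | 47.1% |

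The first two rows share one effect size and count as one scenario. The nominal rate is 5%.

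**4. Illustration of partial compliance.** This simulation rests on different assumptions: n = 34, no true difference, background pain shared by both sides (gamma-distributed, mean 5, 10 or 20 mm), side-specific noise with SD 30% of that mean, and control scores under-reported by a fixed fraction. The paired t test rejected in about 5% of trials with no under-reporting, 30% with 10% under-reporting and 95% with 25%. At a 10 mm background the false mean differences were about 0, 1.0 and 2.5 mm. The rates depend heavily on the assumed noise.

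**5. What remains to be collected.** At submission 24 were enrolled and 14 had completed. That leaves 38 − 24 = 14 participants who could be wholly under new wording, and at most 24 − 14 = 10 with part of their diary under it. For 14 pairs, power at dz = 0.5 is about 41%.

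**The case against.** The strongest reply is that one sentence is not the whole instruction. The section asks for maximum pain on each side, the scale's anchors name no cause, every reading has a cause question that would be nearly redundant if only laceback pain counted, and the training refers to the appliance on left and right. The diary itself is not shown. This stands as far as it goes: many participants may score the control side above zero. It does not remove the problem, because participants who follow the narrow rule drop control pain while others do not, and the net shift still disfavours the laceback. Nor is the training text a clean opposite of the rule, since its examples are ligature and laceback features.

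A reader might infer more than the text supports:

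- **That control scores are fixed at zero and the comparison is simply void.** Zero is the extreme of literal compliance, and other wording in the same section pulls against it.
- **That the T0 baseline must also be zero.** The sentence follows the description of the take-home diary and may govern only that. The article does not say that it applies to baseline.
- **That false positives will run at 85%.** That figure needs one assumed effect size, control at exactly 0 and all 38 participants. A non-negative score whose SD is twice its mean is also strongly skewed, so the Wilcoxon test may be the one used.

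It could also be said that a participant who separates causes perfectly would report just the laceback's own contribution. The plan offers no basis for expecting that of unblinded participants.

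**Conclusion.** The instruction is wrong as written and conflicts with the wording around it. It biases the side-to-side pain AUC comparison towards more pain on the laceback side, fully if followed literally and partly if followed unevenly. The direction follows from the text, on the premise that some background pain is attributed to the laceback. The size does not: the assumed scenarios with control at 0 give about 52% to 85% false rejection at n = 38 and 47% to 81% at n = 34, and less for the same attributed pain if control scores are above 0.

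The damage is confined to pain, which the Abstract and Methods list as secondary, although the Discussion at one point calls it a primary endpoint. The plaque outcome, its sample size and the archwire outcome are unaffected.

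**What to change.** - Delete the sentence. Ask participants to mark the maximum pain or discomfort on each side from any cause, in identical words for both sides and at baseline.
- Bring the training paragraph into line with that wording.
- Keep the existing cause question, and use it only to describe laceback-attributed pain as a separate item.
- Date the change and flag diaries completed under the old wording. Report the pain comparison overall and by instruction version. State that the old-wording data are probably biased against the laceback and that the corrected subset is small (about 14 wholly new participants plus up to 10 partial).

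Resting the between-side conclusion on corrected diaries alone is a debatable trade-off at about 41% power for dz = 0.5, so reporting by version is the more proportionate course.

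The cost is an ethics notification, new diary wording, mixed-version pain data and lower precision for the corrected comparison. Each further participant enrolled under the old wording shrinks the corrected subset.

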### Blinding

The participant and the respective operators providing treatment could not be blinded due to the nature of the intervention. During T_1_, T_2_, or any emergency appointments, laceback complications are first assessed by the principal investigator. This is not blinded, as it is to merely record how many laceback complications occur on the side that has laceback, whereas the contralateral side does not have any laceback. The principal investigator then removes the laceback ligatures. Then, archwire complications and plaque scores are assessed by an orthodontic resident not treating the participant. As such, data collection for archwire complications and plaque scores will be blinded. As the lacebacks are removed by the principal investigator, the assessor is unaware of the site of intervention.

Examiner calibrations were conducted prior to trial commencement for plaque score assessment to ensure good inter- and intrarater reliability among all plaque score assessors. All data are coded and anonymized by the coinvestigator who withholds coding information about treatment allocation from the main data analyst until major analyses are completed. Unblinding is also allowed if a participant withdraws from the trial due to a severe adverse event. The overall study flow is illustrated in Figure 5.

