This study also reflects the broader shift in orthodontic research toward patient-reported outcome measures as primary or coprimary endpoints. Recent studies have emphasized that orthodontic evidence should prioritize outcomes that are directly meaningful to patients, not merely clinician-assessed clinical indices [37-39]. By incorporating pain and discomfort as primary endpoints alongside plaque score and appliance complication rates, this trial provides the more comprehensive evidence base required for evidence-based clinical decision-making and patient-centered consent.

Key strengths of this protocol include its randomized split-mouth design, which controls for patient-level confounders; the use of validated and orthodontically appropriate outcome measures (OPI for plaque and Visual Analog Scale for pain); standardized laceback placement verified against a study model prior to commencement; blinded plaque score assessment; and prospective trial registration (ClinicalTrials.gov ID: NCT07039071). The split-mouth design is particularly advantageous in this context because the intervention is strictly localized: the presence of a laceback on 1 side of the mouth does not mechanically or biologically influence plaque accumulation, archwire stability, or pain on the contralateral side, thereby satisfying the key prerequisite for a valid split-mouth trial with negligible carry-across effect.

Several limitations should be acknowledged. First, the single-center nature of this study, conducted within a specialist postgraduate orthodontic clinic, may limit generalizability to primary care settings or to practices using different bracket systems or prescriptions. Second, the inability to blind participants or the treating clinician to the intervention side is an inherent limitation of the split-mouth design; this risk has been partially mitigated by implementing blinded plaque score assessment. Third, the 8-week follow-up period may not capture longer-term changes in oral hygiene adaptation or pain habituation. Fourth, the use of a single operator for laceback placement enhances consistency and reproducibility within this trial, but may restrict external validity across different clinical hands. These limitations will be transparently reported in the subsequent efficacy paper and will be considered carefully during interpretation of results.

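### The pre-study pain teaching illustrates appliance pain only with laceback hardware, an avoidable cue toward higher laceback-side scores from unblinded participants, and the stated mitigation does not reach pain

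*Protocol article*

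**What the plan says.** All references are to the protocol article.

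- **Blinding:** "The participant and the respective operators providing treatment could not be blinded due to the nature of the intervention". Blinded data collection covers archwire complications and plaque. The main analyst is also kept from the allocation code.
- **Secondary Outcomes: Pain, who scores:** "Pain score is recorded by the study participants on both laceback and no laceback sides".
- **Same section, what to record:** "Participants are informed that the pain recorded should arise from the laceback". Each reading also carries an open-ended question on the cause of pain; the Intended Statistical Analysis gives it no use.
- **Same section, teaching:** "Prior to study commencement, participants will be explained about the different possible causes of pain during orthodontic treatment". Participants are then taught to watch for appliance pain, with two examples: "long ligature wires rubbing on the cheek and twisted ends of laceback, which are pointed and poking on the oral mucosa". They are also asked to find sore areas on the left and the right.
- **Same section, purpose of the teaching:** it answers spill-over of pain between sides, of which the text says "this is minimized through patient education about pain localization". Expectation is not mentioned.
- **Discussion, limitations:** the inability to blind participants and treating clinicians is acknowledged, and "this risk has been partially mitigated by implementing blinded plaque score assessment".
- **Discussion, hypotheses:** the authors expect somewhat more discomfort on the laceback side.

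**The concern.** In a split-mouth trial with an open-label, self-rated outcome, anything that draws attention to one side enters the treatment contrast directly. Pairing does not remove it, because the cue differs between the two halves of the pair. Knowing the allocation is unavoidable here. The choice of examples in the teaching is not.

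Pain is one of the specific objectives in the Introduction, and the Discussion intends the result for patient counseling. If the teaching raises laceback-side scores even by a few millimetres, a positive pain result becomes hard to interpret, because the bias runs in the hypothesized direction. The limitations paragraph could then reassure a reader wrongly, since the mitigation it names belongs to another outcome.

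**Working it through.** **Step 1. Do the two examples apply to both sides?**

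| Item | Laceback side | Control side | Where stated |
|---|---|---|---|
| Long steel ligature | Yes: the laceback is tied from a preformed long ligature | No: archwires are held by elastomeric modules | Standardization of Laceback Placement; Interventions Common to Both Groups |
| Twisted laceback end | Yes: a 3 mm pigtail at the canine | No | Standardization of Laceback Placement |
| Bracket edges | Yes | Yes | Introduction, as a cause of mucosal ulceration |
| Archwire ends | Yes | Yes: cut flush, not cinched | Introduction; Interventions Common to Both Groups |

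The two sources used as examples occur on the intervention side only. Two that the Introduction itself names, and that occur on both sides, are not used.

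**Step 2. Does any stated safeguard act on the pain score?** Blinded plaque scoring and blinded archwire assessment act on other outcomes. Analyst blinding acts after the score has been recorded. The teaching is aimed at localization. The cause-of-pain question might describe attribution, but no analysis uses it. None of these limits expectation in the rating.

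**Step 3. The plan's own figure.** The only sample-size calculation is for plaque. A paired t test with d = 1/1.88 = 0.532 and two-sided 5% gives n = 34 with power 85.3%, so the stated 34 reproduces. It says nothing about pain: no SD, target difference or power is given for pain AUC. Only n = 34 is carried forward.

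**Step 4. Illustration of size. The shifts and SDs are assumptions.**

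Diary times after the visit are 4 h, 24 h, 3 days, 1, 2, 3 and 4 weeks (Secondary Outcomes: Pain). Suppose every reading after T0 on the laceback side is raised by b mm, and the T0 reading, taken before placement, is not. By the trapezoidal rule the first interval (4 h = 1/6 day) counts half, so

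added AUC = b × (28 − 1/12) = 27.917 × b mm-days.

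- b = 2: 55.8 mm-days
- b = 5: 139.6 mm-days

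The plan averages the T0–T1 and T1–T2 AUCs. If the second period starts from a shifted reading, its added AUC is 28 × b (56 or 140), so the average hardly changes. The SD below is that of the paired difference in the averaged AUC.

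With no true effect, the paired t statistic has 33 degrees of freedom and noncentrality (added AUC / SD) × √34. The two-sided 5% critical value is 2.035.

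| Assumed SD (mm-days) | b = 2: noncentrality | P<.05 | b = 5: noncentrality | P<.05 |
|---|---|---|---|---|
| 250 | 1.302 | 24% | 3.256 | 88% |
| 400 | 0.814 | 12% | 2.035 | 51% |
| 600 | 0.543 | 8% | 1.357 | 26% |

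A shift that fades costs less. For example, 5 mm through day 7, then falling to zero at day 14, adds 5 × (7 − 1/12) + 5 × 7/2 = 34.6 + 17.5 = 52.1 mm-days in that period, close to a constant 2 mm.

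**Step 5. The same result without units.** If the shift is expressed in SDs of the paired difference, the test rejects in 9% of trials at 0.1 SD, 21% at 0.2 SD, 40% at 0.3 SD and 81% at 0.5 SD (n = 34).

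**The case against.** The strongest reply has four parts.

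1. **The teaching is broader than its examples.** It covers different causes of pain, asks about both sides, and introduces the laceback items only as instances. The script itself is not shown and may include bracket edges and archwire ends. This stands, and it limits the point to the examples the article reports. A reader might infer that the whole script is about lacebacks; the text does not support that.

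2. **Expectation is unavoidable and disclosed.** Participants see the laceback, risks are explained at consent, and the limitation is acknowledged with a claim of partial mitigation only. This also stands. No change of wording makes pain a blinded outcome. It does not justify an extra one-sided cue, and the mitigation sentence still offers nothing for the outcome most exposed.

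3. **The magnitude does not isolate the teaching.** Correct. Shifts and SDs are assumed, a constant shift over four weeks is a simplification, and the figures show what any reporting bias of that size would do. A reader might infer that the script alone could produce a positive pain result. The document does not support that: the script's share cannot be separated from the open-label effect or from the instruction on which pain to record.

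4. **That instruction is the larger problem.** Telling participants that recorded pain should come from the laceback pushes control-side scores toward zero, since there is no laceback there. This is fair, and the two should be corrected together. Correcting the instruction alone would still leave the one-sided examples in the teaching.

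**Conclusion.** The point holds in a limited form. Unblinded participants rate both sides after teaching whose two reported examples exist on the intervention side only, and no stated safeguard acts on the rating. The likely direction is toward higher laceback-side pain, which is also the authors' hypothesis. That direction is an inference from the design; the amount cannot be derived from the document.

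Under the assumed shifts of 2 to 5 mm and SDs of 250 to 600 mm-days, the false-positive rate ranges from 8% to 88% instead of 5%. The width of that range is itself the message: nothing in the document shows that a small shift would be harmless.

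The primary plaque comparison is unaffected. Pain is secondary in the Abstract and Methods. The Discussion calls it a primary endpoint, a separate inconsistency that makes clean interpretation more important. The change is worth making while enrolment is open, but this is not a flaw that invalidates the trial.

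**What to change.** 1. **Teaching, for participants not yet enrolled (14 of 38 at submission).** Use examples found on both sides, such as bracket edges and archwire ends, with an identical prompt for left and right. The laceback need not go unmentioned: participants see it, have had risks explained at consent, and check the appliance for breakage twice daily. The aim is symmetry. If the script in use is already balanced, correct the article's description instead.
2. **Attribution instruction.** Change it at the same time, so that both sides are rated for the same kind of pain.
3. **Record keeping.** Log which script each participant received and describe the pain contrast by script version. Do not treat this as a test of bias: with 24 against 14 participants and an SD of 250 mm-days, power is about 10% for a 2 mm difference between scripts and 37% for 5 mm.
4. **Discussion, limitations.** State that blinded assessment protects plaque and archwire outcomes only, and that the pain comparison is open-label, self-reported and may be inflated by expectation.

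Cost: a revised script, a short ethics notification and one or two sentences of text. The drawback is that pain data are then collected under two scripts. Each participant's left-right comparison stays within one script, so the paired analysis remains usable.
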